## Abstract

**Background:**

People 65 years or older are at greater risk of serious complications from the seasonal influenza compared with young. To promote elderly people’s behavioral compliance toward influenza prevention, the aim of the current project is to develop, implement, and evaluate a theory-based low-administration-cost intervention building on a leading psychological theory, the Health Action Process Approach (HAPA).

**Methods:**

The target group is Hong Kong Chinese elderly people aged 65 or older who rarely or never adopt any preventive actions. This project will be conducted in three phases over 24 months. In phase 1, intervention program will be developed building on the HAPA theoretical framework which comprises both the initiation and maintenance of influenza prevention behaviors. In phase 2, intervention will be implemented and evaluated using a randomized controlled trial, including: (a) behavior initiation only, (b) behavior initiation + behavior maintenance, and (c) control group. Both the initiation and maintenance components will comprise weekly-delivered telephone-based individual intervention sessions in 3 months. In phase 3, outcome evaluation of behavioral and psychological variables and process evaluation will be conducted. The effectiveness of the intervention will be analyzed using a series of linear mixed models on each behavioral and psychological outcome variable. Structural equation modelling will be used to test the hypothesized theoretical sequence in the HAPA model.

**Discussion:**

The proposed project is expected to design theory-based intervention materials to promote the influenza prevention behaviors in Hong Kong elderly people and provide information on its effectiveness and the potential changing mechanism of behavior initiation and maintenance.

**Trial registration:**

This randomized controlled trial was funded by the Health and Medical Research Fund (HMRF), Food and Health Bureau of the Government of the Hong Kong Special Administrative Region (Ref: 16151222) and was registered on 13/10/2017 at CCRB Clinical Trials Registry of the Chinese University of Hong Kong, a Partner Registry of a WHO Primary Registry (Ref: CUHK_CCRB00567).

## Background

Seasonal influenza can cause mild to severe illness, or even death. Each year, approximately 1 million deaths worldwide are estimated to be related to influenza [1]. According to the American Center for Disease Control and Prevention [2], certain groups of people, such as children under five, elderly people aged over 65, pregnant women, and people with certain chronic medical conditions, are at high risk of seasonal flu-related complications. It has been reported that Hong Kong elderly people (age above 65) are 14 times more likely than midlife adults (age between 40 and 65) to die from influenza [1]. Based on an assessment of weekly hospitalization counts in Hong Kong during 1996 to 2000, influenza was revealed to be significantly associated with hospitalization for acute respiratory disease, with large and noticeable rates of excess hospitalization for elderly people aged above 65 [3]. In peak influenza season, these individuals are more vulnerable to influenza. As such, elderly people are an ‘at risk’ population, given the fact that the population is, in general, aging and is going to increase massively in the future. This leads to the prevention of illness in this population a priority for governments, otherwise it’s going to cost health services a massive amount. To prevent infection with seasonal flu, people are advised to maintain some key prevention behaviors, such as wearing facemasks in enclosed public spaces, hand washing, using antibacterial sanitizers, or to consider having an influenza vaccination [4].

According to the concept of bounded rationality [5], individuals in influenza pandemic make decisions on health care and medication using heuristics, or rules based on past experiences and information instead of using rational decisions. Therefore, it is necessary to provide individuals a theory and evidence-based intervention to guide them form rational decisions when facing an influenza pandemic. Research adopting social psychological theories in influenza prevention has generally focused on influenza vaccination behaviors examining perceived severity, perceived barriers, perceived susceptibility, and perceived benefits, as well as social norms, intentions, worries and regrets towards vaccinations [6–11]. There are several theoretical models to explain the decisions and behaviors on influenza vaccination. For example, the health belief model [12] examines individuals’ perceptions and attitudes towards illnesses or health compromising behaviors in terms of three facets: individual perceptions (i.e., perceived susceptibility and perceived severity), modifying factors (i.e., perceived threat, environmental factors, and cues to action), and likelihood of action (i.e., perceived benefits and perceived barriers). Previous studies have provided initial support for the predictive value of these facets on individuals’ acceptance of influenza vaccination [6, 10]. Yet, the risk perception alone cannot fully explain preventive behaviors without considering the influence of outcome expectations and social norms, namely, social pressure of a normative status. The theory of planned behavior [13], on the other hand, explains the influences of individuals’ attitudes, subjective norms, and perceived behavioral control on the intentions and behaviors of influenza prevention. Intention is viewed as the most proximal determinant of individuals’ volitional behaviors. Research has preliminarily demonstrated significant associations between these beliefs and intentions to receive the influenza vaccine, which in turn predicted vaccination behaviors [9]; while non-intention to vaccination is significantly related to disbelief in the efficacy of, and negative attitudes toward vaccination as well as lack of perceived threat [7].

Although vaccination is an ideal way to prevent all types of influenza, numerous serotypes and the high variability of the influenza virus still challenge the uptake of influenza vaccines. In addition, everyday preventive actions, such as washing hands, avoid touching eyes, nose or mouth, and facemask wearing also play a very important role in prevention. Moreover, the relationship between vaccination and other influenza preventive behaviors (e.g., personal hygiene practices) is still unknown. Regarding as one of the main factors contributing to the transmission of influenza within the community, low behavioral compliance to these recommended health actions are frequently reported [14] and this might be explained as acceptance of vaccination accidently warrant people a false information/belief of free of being infected, which further causing them to lower their behavioral compliance. Nonetheless, researchers have begun to investigate the psychological factors associated with the lack of behavioral compliance toward influenza prevention [6, 15]. For example, consistent with the health belief model, the reason people fail to, or refrain from, wearing facemasks might be due to a lack of perceived susceptibility, cues to action, and perceived benefits, rather than lack of perceived severity and perceived barriers [15].

Although both the health belief model and theory of planned behavior could somewhat explain the complex cognitive interactions in influenza prevention, the factors of post-intentional volitional stage have been inadequately addressed which play an important role in the maintenance of preventive behaviors. Although the motivational paths to intentions have been well-established with large effect sizes, the prediction from intention to health behaviors always fail, a phenomenon called “the intention-behavior gap” [16]. Based on the model of action phases [17] and social-cognitive theory [18], the health action process approach (HAPA) [16] was developed by integrating these two theoretical approaches. The HAPA stipulates a two-phase approach to action, a motivational phase and an implemental or ‘planning’ phase. Motivation is considered a necessary but not sufficient condition for action initiation and persistence; people also need to identify effective plans to enact their intentions or motives. Interventions should, therefore, target both motivational and implemental phases [19]. In other words, it suggests a distinction between (a) pre-intentional motivational processes that lead to a behavioral intention, and (b) post-intentional process that lead to actual health-related behavior. The HAPA is, therefore, an appropriate approach to explain the processes that lead to motivated behavior and its enactment in health contexts, including the influenza vaccination behaviors [20]. It has also been demonstrated applicable in the local context of Hong Kong for other health-related behaviors such as the condom use for men who have sex with men [21].

The current project therefore will develop a HAPA-based intervention to promote influenza prevention behaviors in Hong Kong older adults. In order to promote the initiation and maintenance of influenza prevention behaviors, it will comprise intervention components targeting both motivation and planning. In the behavior initiation stage, three key psychological variables have been associated with increased motivation toward influenza prevention: risk perception, action self-efficacy, and outcome expectancy. The intervention components that have been shown to target and effect change in each of these variables are information provision (risk perception, action self-efficacy, and positive outcome expectancy), goal setting (action self-efficacy), and mental simulations (positive outcome expectancy). In the behavior maintenance stage, different strategies will be used which include the maintenance/relapse prevention self-efficacy, coping planning, and maintaining the satisfaction and enjoyment of the behavior change. The components targeting increased planning are action plans or implementation intentions [19]. Comparing to the behavior initiation stage which focuses on approaching a more favorable health stage, the maintenance stage help participants avoid reverting to a less favorable non-intending status [22].

### Amis of the current study

In order to increase influenza prevention behaviors in Hong Kong older adults (aged 65 years and over), the aim of this project is to develop, implement, and evaluate a HAPA-based intervention, which comprises two main components of a health behavior change, namely, behavior initiation and behavior maintenance. Four specific objectives will be tested: (a) design and develop an intervention to promote influenza prevention behaviors consistent with guidelines of Department of Health in non-intending older adults; (b) imply the intervention in a sample of older adults in Hong Kong who reported never or rarely adopt influenza preventive measures during the past year using a randomized controlled trial; (c) evaluate the effectiveness and a 6-month sustainability of the intervention to change primary outcome variables (i.e., washing hands, avoid touching eyes, nose or mouth, facemask wearing, and vaccination); and (d) identify the psychological variables (i.e., intention, action and coping planning, maintenance and recovery self-efficacy) responsible for explaining the effect of the intervention.

Five hypotheses will be tested in this project: (a) participants in the two intervention groups (i.e., behavior initiation + behavior maintenance; behavior initiation only) will have significantly higher rates of influenza prevention behaviors relative to participants allocated to the control group; (b) participants in the “behavior initiation + behavior maintenance” intervention group will have significantly higher participation in influenza prevention behaviors relative to participants allocated to the “behavior initiation only” intervention group; (c) participants in the two intervention groups (i.e., behavior initiation + behavior maintenance; behavior initiation only) will report significantly greater action self-efficacy, outcome expectancy, risk perception, and intention than participants in the control group. Participants in the “behavior initiation + behavior maintenance” intervention group will report stronger action and coping planning, maintenance and recovery self-efficacy, and social support than participants in the “behavior initiation only” intervention group and the control group; (d) participants in the “behavior initiation + behavior maintenance” intervention group will report significantly greater action self-efficacy, outcome expectancy, risk perception, and intention, and stronger action and coping planning, maintenance and recovery self-efficacy, and social support than participants in the “behavior initiation only” intervention group; (e) consistent with the propositions of the health action process approach, intention, action and coping planning, maintenance and recovery self-efficacy will mediate the effect of the intervention condition on influenza prevention behaviors.

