## Methods

### Participants

Participants in the current study will comprise Hong Kong Chinese older adults. Participants will be eligible if they are 65 years or over; retired or homemakers; willing to be randomly assigned to experimental or control groups; able to understand the study rationale; a first-language Cantonese-speaker; and, most importantly, non-vaccinated within 1 year and report never or rarely adopting any of the influenza prevention behaviors listed by the research group. Participants who report more frequent preventive behaviors will not be invited to attend the preliminary session. We will also exclude older adults who are dementia as well as who are fragile to move.

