#### Telephone-delivered individual behavior initiation sessions

Participants in (a) “behavior initiation” and (b) “behavior initiation + behavior maintenance” intervention groups will receive telephone-delivered intervention sessions at weekly intervals throughout the course of behavior initiation for 3 months. The purpose of these is to serve to remind participants of their influenza prevention goal and their action plans to implement them, mainly focused on the motivational stage. The intervention sessions will be administered by telephone lasting 10 to 20 min, and will be audio-recorded with the permission from participants for fidelity checks. To the extent that participants will have talked about their appropriate influenza prevention goals in the goal setting, mental simulation, and action planning exercises, step-by-step personal instructions and feelings about pursuing their goal, and when and where they will pursue their goals. Participants in the control group will not receive the telephone-delivered intervention sessions. Part-time research assistants will be recruited to deliver the telephone intervention sessions appropriately 10–15 min. They were be trained by, and receive feedback from, the PI and project coordinator and practice with each other in simulated scenarios.

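### Objective (a) names non-intending older adults, but enrolment selects on behaviour and vaccination only, so the arm contrasts cannot by themselves support a statement about non-intenders

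*Protocol article*

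**What the plan says.** The protocol article describes the target group in two ways.

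- **By intention.** In the aims section, objective (a) is to develop an intervention to "promote influenza prevention behaviors consistent with guidelines of Department of Health in non-intending older adults".
- **By behaviour.** Objective (b), in the same sentence, tests the intervention in older adults "who reported never or rarely adopt influenza preventive measures during the past year using a randomized controlled trial". The abstract describes people "who rarely or never adopt any preventive actions". The Participants section requires people to be "non-vaccinated within 1 year and report never or rarely adopting any of the influenza prevention behaviors listed by the research group", and adds: "Participants who report more frequent preventive behaviors will not be invited to attend the preliminary session".

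Neither the Participants section nor the description of the preliminary session screens on intention. Intention is among the psychological measures listed under Baseline measures.

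Under Data analysis, each linear mixed model adjusts for the baseline score of its own dependent variable and for demographic variables. The structural equation model includes demographic and baseline variables more generally.

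**The concern.** In the Health Action Process Approach, not intending and not acting are different states. The Background separates processes that lead to an intention from those that turn it into action, and it supports this with the intention-behaviour gap: "the prediction from intention to health behaviors always fail". It also uses non-intending as the name of a stage. A person who rarely washes hands or wears a mask may therefore already intend to, and a screen on behaviour cannot tell the two kinds of person apart.

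Two things are at stake. The first is interpretation: a pooled result describes inactive, unvaccinated older adults, not the group that objective (a) names. The second is sensitivity on intention. The initiation calls are "mainly focused on the motivational stage", and intention is an outcome in hypotheses (c) and (d) and a mediator in hypothesis (e). Anyone who already intends has less room to gain on that scale.

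**Working it through.** **1. Definitions side by side**

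| Place in the article | Defined by | Intention criterion |
|---|---|---|
| Objective (a) | intention | yes, by name |
| Objective (b) | behaviour | none |
| Abstract, Methods | behaviour | none |
| Participants | behaviour and vaccination | none |

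Only objective (a) uses intention. By the Background's theory, the behavioural definition admits both non-intenders and inactive intenders.

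**2. Where baseline intention enters the analysis**

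- Mixed model for intention: yes, as the baseline of the dependent variable.
- Mixed models for the behaviours: no.
- Structural equation model: baseline variables are included, without restriction to the outcome's own baseline.
- Interaction of baseline intention with condition: not stated.

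**3. The plan's own figures**

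The Sample size section uses d = .20, alpha .017, power .90, 65 per group at follow-up and 25% attrition. The attrition step reproduces: 65 / (1 − .25) = 86.7, rounded up to 87, and 3 × 87 = 261. The figure of 65 cannot be checked, because neither the correlation among the four measurements nor the effect tested is stated. The present point does not depend on it.

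**4. Possible dilution on intention (assumed inputs)**

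Let q be the share of enrolled people who already intend. Assume that their intention does not change and that the within-group SD is unaffected by the mixture. Then

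- pooled d = d × (1 − q)
- sample size for equal power multiplies by 1 / (1 − q)²

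The protocol's d = .20 stands in for the effect in non-intenders:

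| q (assumed) | pooled d | multiplier of n |
|---|---|---|
| 0 | .20 | 1.00 |
| 10% | .20 × .90 = .18 | 1 / .81 = 1.23 |
| 25% | .20 × .75 = .15 | 1 / .5625 = 1.78 |
| 50% | .20 × .50 = .10 | 1 / .25 = 4.0 |

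For a sense of power, one set of assumptions that returns a total of 195 is a between-group F-test with Cohen's f = .20 and a correlation of .3 over four measurements. Its noncentrality is .04 × 195 × 4 / 1.9 = 16.4, and its power is .904. Scaling f by (1 − q) gives power .819, .628 and .263 at q = 10%, 25% and 50%. The article does not say that this is the calculation used, so these values are illustrative only.

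**The case against.** The strongest reply is that objective (a) is a development aim for phase 1 and does not define the trial sample. Objective (b), the abstract and the eligibility criteria agree with each other, and none of the five hypotheses mentions non-intenders. This largely stands: the trial population is clear, and the slip is in one objective. But this trial is the only stated test of the intervention that objective (a) describes, so the wording invites a conclusion the sample cannot carry.

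A second reply is that inactive intenders are a legitimate target. The initiation package includes implementation intentions, and phase 1 aims to help people convert motives into action. This also stands. Any dilution therefore bears on intention more than on the behaviours, which are the primary outcomes.

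A third reply is that subgroup rules and optional covariates belong in an analysis plan. Their absence alone would be no finding. They are raised here only as the way to deal with a contradiction that the article itself contains.

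A reader might go further and infer three things that the documents do not support:

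- **That intenders are enrolled and the effect is diluted, as fact.** The article gives neither their share nor their change in intention. The Background says that intention predicts behaviour poorly, not that many inactive people intend to act.
- **That the comparison of arms is biased.** Randomisation protects it.
- **That the plan ignores baseline intention.** It is a covariate in the intention model, and baseline variables enter the structural equation model.

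**Conclusion.** The inconsistency is real and needs no assumption: objective (a) names a population that the eligibility criteria do not select. The arm contrasts remain valid for the behaviour-defined population. What they cannot do alone is support a statement about non-intenders. A wrong attribution would arise only if the results were reported as applying to that group.

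Dilution of the effect on intention is a conditional risk. It ranges from none, if no intenders are enrolled, to a halved effect if half already intend and none of them changes. The planned d = .20 is not stated to be an effect in non-intenders, so no loss against the trial's own plan is shown. The remaining analytic gap is narrow: the mixed models for behaviour omit baseline intention, and no analysis asks whether the effect varies with it.

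**What to change.** 1. Reword objective (a) so that it refers to older adults who never or rarely adopt preventive behaviours, matching the Participants section.
2. Add the baseline intention score, which is already collected, as a covariate in the mixed models for behaviour.
3. Pre-specify one secondary analysis, for behaviour and for intention: the interaction of baseline intention with condition, with the score kept continuous.
4. Base any claim about non-intenders on that analysis only.

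A subgroup defined by a cut-off is not recommended. The article offers no cut-off, and splitting arms of about 65 would leave imprecise estimates.

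No new data are needed. The cost is one change of wording and a few model terms. The interaction will be estimated imprecisely at this sample size, so a null result should not be read as showing that the effect is the same at all levels of intention.

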## Methods

### Participants

Participants in the current study will comprise Hong Kong Chinese older adults. Participants will be eligible if they are 65 years or over; retired or homemakers; willing to be randomly assigned to experimental or control groups; able to understand the study rationale; a first-language Cantonese-speaker; and, most importantly, non-vaccinated within 1 year and report never or rarely adopting any of the influenza prevention behaviors listed by the research group. Participants who report more frequent preventive behaviors will not be invited to attend the preliminary session. We will also exclude older adults who are dementia as well as who are fragile to move.

